##### COVID-19

Nine questions created by our research team regarding COVID-19 are included to assess the impact of the pandemic on participants’ experience of anxiety. Participants are asked questions relating to their experience and concerns related to COVID-19 (e.g., “How concerned are you about the potential impact of COVID-19 on your childbirth experience?”; “How much of an impact is COVID-19 currently having on your ability to receive support care for your children?”). Participants are asked to select a response ranging from “Not at all” to “Extremely.”

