#### Diagnostic interviews

##### **Diagnostic Assessment Research Tool (DART)** [90]

The DART is a psychometrically sound, semi-structured diagnostic interview designed to assess of a wide range of mental health conditions within the Diagnostic and Statistical Manual of Mental Disorders – 5th edition – Text Revision (DSM-5-TR) mental health conditions, including all the anxiety and anxiety-related disorders [90]. The DART includes mandatory, criterion-based questions and optional questions that may be necessary for clarification in order to make a diagnosis. Psychometric testing of the DART demonstrates excellent construct validity and good convergent and discriminant validity, and high interrater reliability [91]. The DART is used in this study to assess: (a) all DSM-5-TR anxiety disorders, (b) OCD, (c) PTSD, as well as (d) disorder age of onset and relation to reproduction. To assess perinatal AD specifically, the DART interview has been tailored to include perinatal specific examples (e.g., fear of childbirth, perinatal-related obsessions, birth trauma).

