##### Interview training

Our team has extensive experience training students to administer diagnostic interviews to perinatal research participants. All study interviewers are trained to a strict criterion. Specifically, they are required to match the supervising interviewer: (a) on the primary diagnosis, and (b) to within ± 0.5 severity point, on two successive interviews to be permitted to interview independently. Study interviewers are also trained in special considerations in the assessment of perinatal AD, and the assessment of perinatal specific symptoms of the AD (e.g., worries about the baby, fear of childbirth). Study interviewers are closely supervised throughout the study.

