##### **Perinatal Anxiety Screening Questionnaire (PASQ)** [117]

The PASQ is a newly constructed screening tool, created by our study team specifically for perinatal AD screening [117]. The PASQ screens for all core AD (PD, SAD, SP, GAD, AG, separation anxiety), as well as OCD and PTSD. The tool includes 8 primary “yes/no” questions to probe for the core feature of each AD (e.g., “Do you worry a lot about many different things [e.g., your pregnancy or baby, parenting ability, family finances, work or school, or world events]?”). For each AD, if the participant selects “yes” to the primary question, the next question for that AD section is asked. However, if the participant selects “no” to the primary question, they will move to the next AD section and will be asked a new “yes/no” primary question for a new AD. The PASQ has a total of 36 possible questions, and the number of questions for each AD section varies depending on the number needed to effectively address the core DSM-5 diagnostic criteria of each AD. There are 3 possible questions for SP, 6 for PTSD, 7 for OCD and the remaining AD sections (SAD, PD, AG, GAD, separation anxiety) all have 4 possible questions each. This tool was created for the current project to include examples and descriptions catered to new and expectant parents.

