#### Additional analysis

We will use log-binomial models to evaluate the relative risk of AD with respect to important demographic and reproductive variables (e.g., age, and parity), COVID-19 related concerns, and gender role burden (e.g., time spent in childcare and domestic tasks). We will evaluate these variables as risk factors for AD development and exacerbation. In the unlikely event that none of the assessed screening tools meets the standard of a sufficiently accurate measure, data from the first assessment will be used to empirically derive a new measure. This would involve exploratory and confirmatory factor analysis, followed by logistic regression and prediction modelling, using the screening tool items from the first assessment as training, and the second assessment as testing and validation.

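### COVID-19 concern ratings are to be read as risk factors for AD, although current anxiety alone could produce the association with no pandemic effect

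*Protocol article*

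**What the plan says.** The COVID-19 section of the protocol article describes nine items that "are included to assess the impact of the pandemic on" participants' anxiety. Two are quoted. One is a concern rating: "How concerned are you about the potential impact of COVID-19 on your childbirth experience". The other asks about a reported impact: "How much of an impact is COVID-19 currently having on your ability to receive support care for your children". Responses run from not at all to extremely.

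Under Additional analysis, the plan states: "We will use log-binomial models to evaluate the relative risk of AD with respect to important demographic and reproductive variables". COVID-19 related concerns are named among the explanatory variables, and the next sentence fixes the reading: "We will evaluate these variables as risk factors for AD development and exacerbation".

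The outcome comes from the DART interview. It was tailored with "perinatal specific examples (e.g., fear of childbirth, perinatal-related obsessions, birth trauma"), and the Interview training section gives "worries about the baby, fear of childbirth" as perinatal-specific symptoms of AD. The abstract says the interviews assess current disorders. Procedures places each interview 2 to 6 weeks after the questionnaires.

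**The concern.** A rating of how concerned someone is about childbirth is partly a rating of how anxious that person is. Here it serves as the exposure for a diagnosis of current AD, from an interview that draws on fear of childbirth. Someone who already has AD when filling in the questionnaire is likely to score higher on concern and to be diagnosed a few weeks later. The questionnaire comes first, but that does not settle the direction, because the disorder may predate the rating.

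The relative risk therefore cannot separate two accounts: that pandemic concern led to AD, or that anxious people report more concern. The plan commits to the first by its risk-factor wording and by the stated purpose of the items. The study could publish COVID-19 concern as a risk factor for perinatal AD on a result that is also expected when the pandemic had no effect.

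**Working it through.** The plan states no effect size or power for this analysis, so there is no figure to reproduce. The check asks what relative risk is expected when the pandemic effect is zero.

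**Inputs from the protocol article:** AD prevalence about 20% (abstract); 1,000 participants per time point (Sample size estimation).

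**Assumptions, not in the documents:** anxiety severity and concern are bivariate normal with correlation ρ, which arises only because anxiety raises the rating; AD is severity in the top 20%; high concern is the top 25%; ρ runs from 0.1 to 0.5.

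**Whole sample, current AD.** Let p = P(AD and high concern). Then

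- risk if high concern: r1 = p / 0.25
- risk otherwise: r0 = (0.20 − p) / 0.75
- RR = r1 / r0
- SE(log RR) = √[(1 − r1)/(250·r1) + (1 − r0)/(750·r0)]
- chance of two-sided p < 0.05 ≈ Φ(log RR / SE − 1.96), plus a negligible opposite tail

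Example, ρ = 0.2: p = 0.0688, so r1 = 0.275, r0 = 0.1312/0.75 = 0.175 and RR = 1.57. SE = √(0.0105 + 0.0063) = 0.130; log RR = 0.454; 0.454/0.130 ≈ 3.50; Φ(3.50 − 1.96) ≈ 0.94.

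| ρ | RR, top quarter vs rest | Chance of p < 0.05 |
|---|---|---|
| 0 | 1.00 | 5% |
| 0.1 | 1.26 | 39% |
| 0.2 | 1.57 | 94% |
| 0.3 | 1.96 | nearly 100% |
| 0.4 | 2.46 | nearly 100% |
| 0.5 | 3.12 | nearly 100% |

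A prevalence of 17% or 21% gives similar values. A more extreme contrast, top versus bottom quarter, gives 1.43 at ρ = 0.1 and 2.1 to 8.2 for ρ = 0.2 to 0.5. The protocol names neither contrast.

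**Participants free of AD prenatally, outcome postpartum AD.** Further assumptions: severity correlates 0.6 between the two assessments; concern is linked to postpartum severity only through prenatal severity; all 1,000 have both assessments. That leaves 0.80 × 1,000 = 800 people, 200 in the top quarter of concern and 600 in the rest. By simulation, about 12.6% of them have postpartum AD.

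| ρ | Risk, top quarter | Risk, rest | RR | Chance of p < 0.05 |
|---|---|---|---|---|
| 0.1 | 13.4% | 12.3% | 1.09 | 7% |
| 0.2 | 14.3% | 12.0% | 1.18 | 13% |
| 0.3 | 15.1% | 11.8% | 1.29 | 24% |
| 0.4 | 16.0% | 11.5% | 1.40 | 40% |
| 0.5 | 17.0% | 11.1% | 1.52 | 58% |

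Top versus bottom quarter gives 1.3 to 2.1 for ρ = 0.2 to 0.5, significant in about 17% to 74% of studies.

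Most of the spurious effect thus comes from using current AD in the whole sample. A smaller part remains among people without prenatal AD, because concern also marks sub-threshold anxiety.

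**The case against.** Several counter-arguments have force.

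- **The size is assumed.** No document gives the correlation. At 0.1 the whole-sample result is significant in only about 40% of studies, and among prenatally AD-free people it often is not significant at any value tried. A reader might infer that the model is bound to return a large, significant relative risk; the documents do not support that.
- **The overlap is partial.** The diagnosis follows DSM-5-TR criteria, and fear of childbirth is an added example and a training topic. The COVID-19 item asks about the pandemic's effect on the childbirth experience, which is related but different content. It would go too far to say that exposure and outcome are the same thing. The PASQ also asks "Do you worry a lot about many different things" and gives pregnancy or baby as an example, but it is a screening tool under test, not the outcome.
- **Only two of nine items are quoted, and one is an impact item.** The plan's phrase may be shorthand for the whole set. Scoring and covariates may properly sit in a fuller document, so their absence here is no fault.
- **The repair is imperfect.** Impact items are self-rated and may also rise with anxiety. Concern could be a genuine pathway from pandemic to anxiety, so adjusting for GAD-7 might remove real effect.
- **The analysis is secondary.** COVID-19 appears in none of the listed objectives.

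These points limit the size and reach of the concern. They leave standing the stated risk-factor reading of concern ratings against current AD, which the design cannot support.

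**Conclusion.** The concern holds in a limited form. The plan names concern ratings as explanatory variables for AD and commits to a risk-factor reading. At least one of these ratings overlaps with what the diagnostic interview explores, and the outcome is current disorder. Any positive correlation between current anxiety and the rating gives an expected relative risk above 1 without a pandemic effect. That direction needs no particular value of the correlation; the size does.

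Under the assumptions shown, the relative risk for the top quarter of concern versus the rest is about 1.3 to 3.1 in the whole sample, significant in about 40% to nearly 100% of studies. Among prenatally AD-free people it is about 1.1 to 1.5 and often not significant.

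The point concerns concern-type items in an additional analysis. A reader might infer that it weakens the study's main results; it does not, since no screening metric, cut-off or tool recommendation depends on it.

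**What to change.** In Additional analysis:

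1. Report the COVID-19 concern items as correlates of current AD, without risk-factor wording and without a claim about the pandemic's impact.
2. Limit candidate COVID-19 risk factors to the experience and impact items, and note that these too are self-rated.
3. If a prospective statement on concern is wanted, relate prenatal concern to postpartum AD among participants without prenatal AD. Show results with and without adjustment for the prenatal GAD-7 score, which Table 1 lists as collected, and call the result an association.

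The cost is a change of wording and one extra covariate; no new data are needed. The downsides are that concern no longer yields a risk-factor claim, and that GAD-7 adjustment may remove part of any real effect, which is why both results should be shown.

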### Current status

Recruitment, data collection and study interviews are currently underway and are set to finish in January 2025. To date, we have recruited approximately 60% of our sample, with 783 participants enrolled. Of the 727 enrolled, 316 of these have fully completed their participation in the study.

### Data analysis plan

#### Descriptive statistics

Descriptive information will be presented as means, standard deviations, percentages, and 95% confidence intervals. The diagnostic accuracy of screening tools will be assessed via receiver operating characteristic (ROC) curve analyses within the prevalence sample. AUC values, derived from the ROC curves, represent overall diagnostic accuracy, and will be reported with 95% confidence intervals. Optimal cut-off values for each measure will be determined from ROC analyses and based on maximizing Youden’s *J* index value (see screening tool metrics above). The sensitivity, specificity, PPV and NPV, LR ± , and percent correct classification will also be reported. We will also determine the cut-point associated with 0.75 sensitivity and calculate the corresponding *J* index and specificity (prevalence sample). We will estimate sensitivity and specificity of each of the screening tools for the individual AD.

#### Research objectives

AUC will be compared among all pairwise combinations of tools using DeLong’s method for paired ROC curves [123] and using a false-discovery-rate correction (FDR, with family-wise alpha = 0.05) for *p*-values [124] to account for multiple testing. Sensitivity and specificity will be compared across all tools using McNemar’s test for paired categorical data, with FDR correction for multiple testing [124].

We will report the full composite of the screening tool metrics (i.e., AUC, *J* index, PPV, NPV, LR + , and LR-) for each of the measures assessed. Screening metrics will be reported for the core AD with and without PTSD and OCD, as well as separately for major ethnic and parity groups (i.e., parity = 0, and parity ≥ 1). We will recommend screening tools based on their accuracy (i.e., scores on the above metrics) and implementation feasibility (i.e., length, administration time, scoring time and complexity, and cost, if any). To ensure the screening tools are not missing any individual AD by analyzing them together, we will also estimate sensitivity and specificity for each AD by comparing those who report symptoms meeting criteria for one specific AD with those whose symptoms fail to meet criteria for any AD.

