## Introduction

For many health conditions, screening is the first step in a pathway to effective, and in some cases lifesaving, interventions [1–3]. It allows for population level early disease detection thereby identifying those in need of further assessment and ultimately treatment. Further, screening provides significant cost savings [4–8] by ensuring that only those who require more time and labour-intensive diagnostic assessments are offered them [4, 8–10]. Although screening for mental health conditions has been shown to lead to improved mental health even in the absence of a clear pathway to treatment [11, 12], there are still several gaps in screening for mental health conditions in Canada, particularly in the perinatal period [13].

The current edition of the Diagnostic and Statistical Manual of Mental Disorders (DSM-5) [14] includes ten anxiety disorders and several anxiety-related disorders (AD). For the purposes of this research, we have defined AD to include all DSM-5 anxiety disorders as well as two anxiety-related disorders: posttraumatic stress disorder (PTSD) and obsessive–compulsive disorder (OCD) [14]. The AD affect one in five pregnant and postpartum people [15], and are of high importance for perinatal people both due to the fact that they are highly prevalent, but also because they are associated with a range of negative reproductive health outcomes [15–17]. These include: obstetrical (e.g., miscarriage, low birth weight, preterm delivery) [16, 18–21]; fetal and infant (e.g., impaired self-regulation and motor development, and an increased risk for attention-deficit/hyperactivity disorder) [16, 22–28]; and the birthing parent (e.g., postpartum depression, reduced employment capacity, unemployment, and decreased social, emotional and physical functioning) [16, 17, 29–35]. The AD are also associated with significant health care costs and increased health care service utilization [36–39].

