### Sample size estimation

Approximately 44,000 residents of BC give birth each year [86]. We are seeking a sample of 1,000 participants for each of the two study time points. This will provide 80% power to detect AUC for ROC curves ≥ 0.56 as significantly different from 0.5, at a significance level = 0.05; 88% power to detect sensitivity ≥ 0.60 as > than 0.5; and > 99% power to detect specificity ≥ 0.60 as > 0.5. We will be able to estimate the prevalence of low prevalence conditions (e.g., 3%) with 1.5% margin of error and 95% confidence. Of note, we will have 80% power to detect AUC ≥ 0.65; 80% power to detect sensitivity ≥ 0.72; and 99% power to detect specificity ≥ 0.72. Allowing for an anticipated attrition of 15%, we are seeking to recruit 1,200 participants. To have 80% power to detect sensitivity ≥ 0.7; and 99% power to detect specificity ≥ 0.6 for the individual AD, we will need ≥ 30 participants per AD in this sample.

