### Assessment tools

See Table 1 for a summary of study measures.

**Table 1 Tab1:** Summary of study measures

Domain	Measure	Method	Location
*Intake*			
Consent			Online
*Prenatal Questionnaire (16–32 weeks’ gestation)*			
Characteristics	Demographic and reproductive history information	Self-report	Online
AD Screening Measures	Perinatal Anxiety Screening Scale (PASS) State-Trait Anxiety Inventory (STAI-Y2) Edinburgh Postnatal Depression Scale (EPDS) Kessler Psychological Distress Scale (K6/K10) Matthey Generic Mood Questionnaire (MGMQ) Antenatal Risk Questionnaire (ANRQ-2A) Generalized Anxiety Disorder (GAD-7) Anxiety Disorders 22 (AD-22) Perinatal Anxiety Screening Questionnaire (PASQ)	Self-report	Online
Other functioning	Insomnia Severity Index (ISI) Covid-19 experience Family Work Quality Questionnaire (FWQQ)	Self-report	Online
*Prenatal Interview (2-4 weeks after prenatal questionnaire completion)*			
Diagnosis and onset (ADs, OCD, PTSD)	Diagnostic Assessment Research Tool (DART for DSM-5-TR)	Diagnostic Interview	Zoom or phone
*Pregnancy Check-In*			
Characteristics	Pregnancy status and birth date	Self-report	Online
*Postpartum Questionnaire (6–16 weeks postpartum)*			
Characteristics	Birthing information	Self-report	Online
AD Screening Measures	Perinatal Anxiety Screening Scale (PASS) State-Trait Anxiety Inventory (STAI-Y2) Edinburgh Postnatal Depression Scale (EPDS) Kessler Psychological Distress Scale (K6/K10) Matthey Generic Mood Questionnaire (MGMQ) Antenatal Risk Questionnaire (ANRQ-2A) Generalized Anxiety Disorder (GAD-7) Anxiety Disorders 22 (AD-22) Perinatal Anxiety Screening Questionnaire (PASQ)	Self-report	Online
Other functioning	Insomnia Severity Index (ISI) Covid-19 experience Family Work Quality Questionnaire (FWQQ) Mental health support seeking	Self-report	Online
*Postpartum* *Interview* *(2-4 weeks after prenatal questionnaire completion*)			
Diagnosis and onset (ADs, OCD, PTSD)	Diagnostic Assessment Research Tool (DART for DSM-5-TR)	Diagnostic Interview	Zoom or phone

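### The pairwise AUC comparisons use a false-discovery-rate correction but are labelled with a family-wise alpha of 0.05, which that correction does not guarantee

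*Protocol article*

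**What the plan says.** Under Research objectives in the Data analysis plan, the protocol article says that "AUC will be compared among all pairwise combinations of tools" with DeLong's method for paired curves, and that the p-values receive a false-discovery-rate correction, specified as "FDR, with family-wise alpha = 0.05". The next sentence covers sensitivity and specificity, compared by McNemar's test "with FDR correction for multiple testing". That sentence gives no level and does not use the family-wise label. The article does not define the error rate anywhere else, and nowhere says that family-wise is meant as a name for the FDR level.

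**The concern.** One parenthesis names a method belonging to one error rate and a level belonging to another. The two rates coincide when all null hypotheses are true, because any rejection is then a false one. They can separate once some nulls are false and several remain true.

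The all-equal case is not the one the study expects. Its Objectives section promises to report the most accurate tool, and the AUCs it cites for its candidates run from 0.71 (one K10 estimate) to 0.94 (PASS).

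What is at stake is how a statement that one tool beats another may be described. Taken literally, the label gives a 5% chance that the whole set of pairwise claims contains any false one, and the named method does not ensure that. The sentence also leaves room for two analyses. One analyst could run an FDR procedure and another a family-wise one, and they could declare different pairs different.

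**Working it through.** **Inputs from the protocol article**
- Tools: nine rows of AD screening measures in Table 1, the last three being "Generalized Anxiety Disorder (GAD-7) Anxiety Disorders 22 (AD-22) Perinatal Anxiety Screening Questionnaire (PASQ"). Pairs: 9 × 8 / 2 = 36. With K6 and K10 counted separately there are 10 tools and 45 pairs. With EPDS and EPDS-3A also separate there are 11 tools and 55 pairs.
- Sample size: "We are seeking a sample of 1,000 participants for each of the two study time points" (Sample size estimation).
- Prevalence: "The AD affect one in five pregnant and postpartum people" (Introduction). This gives about 200 cases and 800 non-cases.

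**Assumptions not in the article**
- The FDR procedure is Benjamini-Hochberg at 0.05; the text does not name one.
- AUC estimates are normal with standard error 0.0175 and correlation 0.6 between tools. The standard error of a difference is 0.0175 × √(2 × (1 − 0.6)) = 0.0157.
- Tests are two-sided, and the pattern of true AUCs is varied as below.

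**Step 1: the plan's own figure.** With all nine tools equal, simulation gives a family-wise error of about 4%. The stated 0.05 is met in that case.

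**Step 2: why it can fail otherwise.** Take two tiers, four tools at one AUC and five at another.
- True differences: 4 × 5 = 20 pairs. Tied pairs: 6 + 10 = 16.
- If the 20 real differences are all detected, the smallest p-value among the tied pairs is compared with about 0.05 × 21/36 = 0.029. The expected number of tied pairs below that is 16 × 0.029 = 0.47, so at least one false claim is quite likely.
- The FDR is still held: its bound is 0.05 × 16/36 = 0.022.
- Holm would compare the same p-value with 0.05/16 = 0.0031, and 16 × 0.0031 = 0.05. Family-wise error is held.

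**Step 3: simulation, 9 tools (36 pairs), Benjamini-Hochberg at 0.05**

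| True AUC pattern | Chance of any false claim | FDR |
|---|---|---|
| All equal | 4% | 4% |
| One inferior (0.70), rest 0.80 | 19–20% | 4% |
| Three tiers (0.70 / 0.77 / 0.84) | 25–26% | 1% |
| Two tiers (0.72 / 0.82) | 29% | 2% |
| One tied pair, rest distinct | 4% | below 1% |
| All distinct | 0% (no true nulls) | 0% |

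In the all-distinct case, the chance of any claim in the wrong direction was 0.3% with AUCs evenly spaced over 0.70–0.86, 1.5–1.6% over 0.74–0.82 and 1.5–1.6% over 0.76–0.80. With a single tied pair the error cannot exceed 5%, because no Benjamini-Hochberg threshold is larger than 0.05.

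**Step 4: sensitivity to the assumptions.** Here the standard errors were computed by the Hanley-McNeil formula for 200 cases and 800 non-cases, with 9, 10 or 11 tools and correlation 0.3, 0.6 or 0.8. Family-wise error was 0.040–0.044 (all equal), 0.18–0.23 (one inferior), 0.23–0.36 (three tiers) and 0.28–0.38 (two tiers). FDR never exceeded 0.044. Holm kept family-wise error at 0.022–0.047 throughout.

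**The case against.** The strongest reply is that this is loose wording. The method is named as a false-discovery-rate correction, a source is cited for it, and the McNemar sentence names FDR again without the family-wise label. The likely meaning is FDR at 0.05 over the family of pairwise tests. That is a fair reading, and under it no planned analysis changes. The label would still be wrong and should be corrected.

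A reader might infer three stronger things, none of which the article supports.

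- *That the family-wise error is in fact several times 5%.* This needs several exact ties alongside real differences. The article gives no AUC pattern for its population, and the AUCs it cites come from different samples and sets of disorders. Different instruments need not tie exactly. With every tool distinct there is no true null to reject, and with one tied pair the error is about 4%.
- *That FDR is the wrong method and Holm is required.* FDR is a legitimate choice for comparing many tools, and nothing in the article demands strong family-wise control.
- *That the recommendations depend on these p-values.* The Introduction sets fixed minimum criteria (AUC ≥ 0.8, Youden's J ≥ 0.5, NPV ≥ 0.8, LR+ ≥ 4.0), and Research objectives bases recommendations on the accuracy metrics and on feasibility. No pairwise significance test is named as the decision rule.

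Deferral to a fuller analysis plan does not answer the point. The article is not silent here; it states an error rate that its named method does not guarantee.

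**Conclusion.** The stated property is wrong as written: an FDR correction at 0.05 does not in general carry a family-wise alpha of 0.05. The practical gap is conditional. With 9 tools, standard error 0.0175, correlation 0.6 and Benjamini-Hochberg, the chance of any false pairwise claim is about 20–30% under the assumed tiers, and about 4% or less when all tools are equal, all are distinct, or only one pair ties. The standard error, correlation, tiers and exact FDR procedure are assumptions. The severity is minor: the use of FDR stands, and what changes is the guarantee that may be attached to a claim that one tool is more accurate than another.

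**What to change.** Delete the family-wise wording and state *FDR controlled at q = 0.05* for both the pairwise AUC comparisons and the McNemar comparisons. In reports, do not describe the pairwise superiority claims as having a 5% family-wise error. This is a change of one or two sentences; it costs nothing and leaves the FDR analysis as planned.

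If the sponsor does intend family-wise control at 0.05, the plan must instead name a procedure that delivers it, for example Holm. This is optional and costs some power on close pairs: Holm's strictest threshold with 36 pairs is 0.05/36 = 0.0014.
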